**Objective 5. Analyze the barriers and enablers of making the outpatient follow-up appointment**
How are outpatient follow-up appointments made?
1. What people are involved (hospitalist, patient, caregiver, case manager, outpatient staff, social work) in making outpatient follow up appointments?
2. How is the appointment made (what time frame, by phone, direct access)?
3. What IT tools are used to make the appointment?
4. What is the criteria for who gets an early spot on the outpatient schedule?
5. What do you do if there is no outpatient provider?
o What proportion of patients do not have an outpatient provider?
6. Would telehealth be possible if the patient does not want to make an office visit?
7. Is there a home physician/NP visiting program available?
8. How is success in making the appointment monitored?
o What proportion of the time are you successful in making the appointments?
9. What are the barriers to making the appointment within 7 days?
10. What are examples of enablers, (staff, IT, patient education, availability) to making the appointment?
11. How are patients and their caregivers involved in making follow up appointments?
12. How is the appointment communicated to the patient and/or family?
13. What are some areas for improvement in making follow up appointments?
14. What strategies were tried and failed in making follow up appointments?
15. What works?
16. Do the insurance companies play a role in facilitating early follow-up? If so, how?
17. To make improvements in this process, who should we work with?
**Objective 6. Determine the process for how home health activates timely visits**
How do you implement timely home visits (defined as: visits within 48 h of hospital discharge)?
1. What people are involved in scheduling the home health care admission visit?
2. Do the home health agency personnel know the expected hospital discharge date?
3. What conflicts arise when trying to schedule timely home health admission visits?
4. What IT tools are used?
5. What criteria is used to prioritize patient visit timing?
6. How is start of care visit timing monitored?
7. What is your current success rate for making the admission visit within 48 h of discharge?
8. What makes this difficult to do?
9. How do you think we could improve the success rate for achieving timely visits?
10. What strategies were tried and failed?
11. What works?
12. What role does geographic area play?
13. What role does the day of the week play?
14. What role does staffing play?
15. Is patient acceptance of timely visits a barrier? (just got home from hospital, don’t want you to visit)
16. To make improvements in this process, who should we work with?
**Objective 7. Determine the typical visit pattern for week one of post-acute home health care**
How are visit timing and frequency scheduled in week one for post-acute patients at home?
1. What people are involved in scheduling week one visits?
2. What IT tools are used?
3. How are the visit patterns communicated to the nurse or schedulers?
4. How is success of timing and frequency of visits during week one of care monitored?
5. What is your current visit pattern in week one for typical patients?
6. What are the barriers to achieving at least two visits in week one?
7. What are the areas for improvement?
8. What strategies were tried and failed?
9. What works?
10. To make improvements in this process, who should we work with?
**Objective 8. Explore how home health personnel can facilitate completion of the outpatient provider follow-up by one week after discharge**
Please describe the role of home health care and the processes used to encourage and help the patient keep their outpatient provider appointment?
1. Who are the people involved in encouraging the patient to attend their outpatient provider visit?
2. Who is involved in helping the patient attend the visit?
3. How is the visit attendance documented?
4. Are any IT tools used, and if yes what is used?
5. How does home health know whether or not the patient has an appointment?
6. What role does the home health provider play in obtaining an appointment for patients in the first week of home health?
7. What role does the home health provider play in facilitating attendance at outpatient appointments for patients in the first week of home health?
8. What is the current success rate for completion of timely outpatient follow-up visits?
9. How is that measured and within what time frame (7 days, 14 days)?
10. What are the barriers to the patient being seen by an outpatient provider by day 7?
11. What are the areas for improvement?
12. What strategies were tried and failed?
13. What works?
14. To make improvements in this process, who should we work with?

### Consolidated Framework for Implementation Research (CFIR) interviews

A CFIR derived interview guide that measure context, process, and implementation determinants was generated by the team using the online resources at www.CFIRguide.org. Examples include: Relative advantage: How does the intervention compare to other similar existing programs in your setting? Peer pressure: To what extent would implementing the intervention provide an advantage for your organization compared to other organizations in the area? Leadership engagement: What kind of support or actions can you expect from leaders in your organization to help make implementation successful? Patient needs and resources: How do you think individuals served by your organization will respond to the intervention? How well will the intervention meet their needs?

The team will train together in administering the CFIR interviews. CFIR interviews may be individual or in groups; implementation mapping (described above) will be done in groups as appropriate to gain consensus and promote team engagement in planning. For example, mapping the workflow for notifying the HHC intake department may be completed with the group of nurses who staff the HHC intake department. All interviews will be recorded. We will catalogue the implementation strategies and workflows suggested, adopted, modified, or discarded by the participating dyads. Data will be entered and stored in Research Electronic Data Capture (REDCap) [85, 86] or NVivo [87] as appropriate.

### Analysis

#### Aim 1, effectiveness of the I-TRANSFER intervention

A key initial task is the identification of all sepsis survivors in the national hospital dataset. Consistent with our prior work, we will use two complementary strategies to identify sepsis survivors. First, we will use the explicit International Classification of Diseases 10th Revision (ICD-10) codes (A40-41, R65.2). Second, we will employ the implicit approach used in our previous study and developed by Angus and colleagues [88] that requires a code for infection and end-organ dysfunction. Among them we will identify the sepsis survivors transitioned from participating hospitals to their partner HHC agency during the study timeframe by merging the Provider of Service File with the claim files.

Each hospital discharge of a sepsis survivor to HHC will represent a separate record on the timeline file. Some Medicare beneficiaries will have more than one index hospital discharge during the study period. Data available will give us the flexibility to define an “index” hospitalization in several ways. Our main approach will be to analyze all eligible hospitalizations followed by HHC and to adjust for the potential effect of clustering at the patient and provider level. We plan to examine the sensitivity of our results to alternative specifications of the “index” hospital stay including analyses based on a single index hospitalization per person.

Deidentified Medicare claims will be the source of information used to construct Aim 1 outcomes of rehospitalization, total hospital days if readmitted and ED utilization. The CMS claims will be stored a secure, password protected site. The CMS approach to identifying hospital readmissions was successfully used in our heart failure and sepsis studies and we will use the same approach to identify readmissions in this study [24, 50]. Observations on sepsis survivors in the baseline period will be used to check balance on covariates identified by the Andersen Behavioral Model. Any remaining imbalance will be considered by including covariates in the hierarchical regression analysis.

In addition to the survivors from the treated dyads in the baseline period, additional control survivors will be used to provide a much larger sample of control observations. These observations will be drawn from the population of Medicare sepsis survivors not being cared for by any of the participating institutions. This sample is unlikely to be balanced on covariates, a priori, with the sample of survivors from participating providers. Therefore, entropy balancing will be used to create sampling weights for these observations to produce balance on covariates. All hierarchical regression analyses will take these entropy balance weights into account. In addition to an intent-to-treat indicator, the regression will include covariates specified by the Andersen Behavioral Model. Inpatient days after the index discharge will be modeled using hierarchical Poisson regression. ED utilization will be modeled using hierarchical logistic regression.

The pragmatic aspects of the study design make it important to conduct various sensitivity and exploratory analyses. Sensitivity analyses will include checks of robustness of findings with and without sepsis survivors who are readmitted shortly after discharge (e.g., within 7 days), those with a resumption of HHC episode, discharges with very short (1 day) or very long hospital stays (30 days or more), and survivors less than 65 years old. Exploratory analyses will include estimation stratified by type of sepsis, sex (as a biological variable), and hospital ownership status.

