The first homecare visit, usually conducted by a registered nurse, is one of the most critical steps of the home care episode [35, 36], and is important for continuity of care [18, 37, 38]. Too often the HHC nurse conducts the admission visit with fragmented, incomplete, or inaccurate knowledge of the patient’s clinical condition [39, 40]. In our prior work, among sepsis survivors readmitted by 30-days, 33% of hospital readmissions occurred within 7 days. Moreover, we found a mismatch between the hospital diagnoses and the HHC diagnoses, indicating HHC clinicians may not know the patient is a sepsis survivor [14]. For hundreds of thousands of sepsis survivors, the most frequent diagnoses in HHC were pneumonia and urinary tract infection, with sepsis ICD codes appearing only 4% of the time [14]. Further, most of the 7-day readmission risk factors identified by our team were noted after the HHC admission [14]. It is too late to wait for the HHC assessment to occur on the first home visit (which could occur several days after hospital discharge and be available to others in the record up to 5 days later). Providing high quality information from the acute care referral source to increase awareness of the sepsis survivors facilitates accurate care planning and supports provision of earlier visits, higher quality care, and prevention of avoidable, early rehospitalization for a sizable and increasing population of sepsis survivors [41–44]. The National Consensus Project Clinical Practice Guidelines for Quality Palliative Care support access to palliative care throughout the trajectory of severe illnesses like sepsis, increasingly in community or home settings. Improving the transfer of information can increase access to these resources, which can enable patients and families to receive support in their homes [45]. For these reasons, our intervention starts in acute care to improve identification of the sepsis survivor and to highlight the diagnosis for HHC clinicians.

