Our I-TRANSFER intervention is designed to address several barriers and gaps that may jeopardize the implementation of early post-acute surveillance. Sepsis survivors are not consistently identified with a medical diagnosis of sepsis until after discharge from acute care [51–55]. This results in the diagnosis and other patient characteristics not being adequately communicated to the next level of care [1, 39, 40, 56]. Home health clinicians likely do not know they are receiving a sepsis survivor. Second, there is little evidence to guide the transition of sepsis survivors to HHC. Our protocol is designed to provide a critically needed, especially post-pandemic, best practice intervention model to clinicians and the HHC industry nationwide. This protocol is even more timely given the pandemic, as research suggests that COVID-19 can lead to sepsis [57] and many hospitalized patients prefer to recover at home due to skilled nursing facility capacity and safety concerns [58]. Third, among sepsis survivors transitioned to HHC, and not readmitted within the first week, only 28% received the early visit protocol, shown by our team to be associated with significantly reduced readmissions [24]. This presents an important opportunity to generate further evidence of effectiveness and inform widespread implementation to help many more sepsis survivors. Our advisory group, comprised of national leaders in sepsis care and HHC professional organizations will facilitate widespread dissemination of our findings, from academic nursing and medicine to industry practitioners.

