Implementation of the I-TRANSFER components will be guided by the stakeholders and research team using intervention mapping, as described below. The context and determinants (barriers, enablers), processes, and strategies encountered during Aim 1 will be collected for Aim 2 analysis. Hospital partners will work with the study and HHC team to achieve the following components of I-TRANSFER: identify the sepsis survivors during the hospitalization, make the outpatient follow-up appointment before discharge, notify the HHC agency of a sepsis survivor, conduct timely home health visits and outpatient visits in week one. Based on our preliminary work, we have identified several effective strategies that we can suggest to better identify the sepsis survivor, including generalizable use of sepsis order sets within the electronic health record [14]. We will also recommend use of the Centers for Disease Control (CDC) Epicenters Sepsis Clinical Surveillance Definition, which has the advantage of identifying confirmed cases of sepsis given the criteria of sustained antibiotic delivery [35, 77, 78]. We will examine fidelity to these recommended components as potential implementation enablers.

Challenges we expect to face in making and achieving a timely outpatient visit are limited appointment availability, and patients who cancel or do not attend the visit. A potential strategy is to increase awareness about I-TRANSFER’s evidence and include a script for the clinician to educate the patient about the value and importance of the outpatient visit. Transportation may be an issue as well and will be brainstormed for solutions with the stakeholders and tracked as a barrier. Hospital based personnel will notify the HHC intake department when the patient is a sepsis survivor. The intervention mapping will determine the workflow for this component with each site. It may include phone calls, text messaging, faxed or electronic documents.

HHC intake personnel will likely schedule the nurse visits and notify the visiting nurse of the sepsis diagnosis and date of the outpatient appointment. To meet protocol, the first registered nurse home visit will occur within 2 days of hospital discharge, with a second visit that week. The patient will be encouraged and assisted if necessary (e.g. transportation) to attend their scheduled outpatient appointment.

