**How are sepsis survivors identified in your hospital?**
1. Who is involved in clinical documentation and coding that the patient has/had sepsis?
o What do you do with the information? How is it shared/alerted and with whom?
2. What IT systems/tools are used?
o How are the IT systems used? (what function do they complete?)
o Criteria used to code sepsis categories?
3. How is success in identifying sepsis patients monitored?
4. What is your accuracy rate for identifying sepsis patients?
o How do you measure accuracy?
5. What are the steps in identifying sepsis patients that you think need improvement? Why?
o What is needed to achieve improvement?
6. What strategies were tried and failed?
7. What are the successful strategies?
8. What are the barriers to identification, IT documentation and communication, accuracy, monitoring accuracy?
9. To make improvements in this process, who should we work with?
10. How is sepsis defined in your hospital?

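### I-TRANSFER can change which partner-hospital discharges meet the claims definition of sepsis, and no planned analysis tests whether the Aim 1 cohort has shifted

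*Protocol article*

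**What the plan says.** **Who is analysed.** The Aim 1 analysis section of the Protocol article gives two routes into the cohort, both read from hospital claims. The explicit route is "First, we will use the explicit International Classification of Diseases 10th Revision (ICD-10) codes (A40-41, R65.2". The implicit route is one "that requires a code for infection and end-organ dysfunction". I read the two as a union, since the article calls them complementary.

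**What the intervention does in hospital.** The Background says "our intervention starts in acute care to improve identification of the sepsis survivor and to highlight the diagnosis for HHC clinicians". Under Study design, the components for hospital partners begin with "identify the sepsis survivors during the hospitalization, make the outpatient follow-up appointment before discharge". The team offers strategies "to better identify the sepsis survivor, including generalizable use of sepsis order sets within the electronic health record", and adds: "We will also recommend use of the Centers for Disease Control (CDC) Epicenters Sepsis Clinical Surveillance Definition". Implementation Mapping treats identification of survivors as a performance objective and expects education, workflow and IT changes, and audit and feedback. Objective 1 of the needs assessment (Table 2) asks "Who is involved in clinical documentation and coding that the patient has/had sepsis", how accurate identification is and which steps need improvement. Objective 4 asks about improving the documentation of sepsis.

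**Who is compared.** The controls are survivors at the partner sites before implementation and Medicare survivors treated elsewhere, the latter weighted by entropy balancing.

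**What is checked.** The sensitivity analyses cover early readmission, resumed HHC episodes, very short or long stays, and age under 65. The exploratory strata are type of sepsis, sex and hospital ownership. The Discussion adds treatment indicators in the retrospective control data and onboarding period, to detect early adoption of the protocol.

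**The concern.** A before-and-after comparison with external controls assumes that the same kind of patient is counted in every period and at every site. Here, entry depends on codes written at partner hospitals while those hospitals are being helped to recognise sepsis better. If recognition changes documentation, and documentation changes claim codes, cohort membership becomes partly a consequence of the intervention.

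The planned safeguards are aimed elsewhere:
- The intent-to-treat indicator assigns exposure within the cohort but cannot protect a cohort whose membership exposure affects.
- Time adjustment and concurrent national controls deal with coding trends common to all hospitals, not with a change confined to the partners.
- Entropy balancing and regression act on patients already selected.
- The early-adoption indicators compare outcomes between periods, not the composition of the cohort.

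At stake are the primary outcome and ED use. A change in who is labelled could be read as an effect of early visits, or could hide one.

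**Working it through.** **Step 1: who could newly enter.** An infection discharge with coded organ dysfunction is already in the cohort through the implicit route, so adding an explicit sepsis code to it changes nothing. The patients who could move in are infection discharges without previously coded organ dysfunction, which either gain an explicit code or have organ dysfunction newly documented.

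**Step 2: inputs.** From the article's Study sample section: a 23% readmission rate, a target reduction of 7 points, and 869 patients per period. The stated relative reduction is reproduced: 7/23 = 30.4%. The number of newly labelled patients and their readmission rate r are not in the document. Both are assumptions, so a range is shown.

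**Step 3: crude shift with no treatment effect.** Let e be extra labelled patients as a fraction of those who would have qualified anyway.

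Rate = (0.23 + e × r)/(1 + e); spurious fall = e × (0.23 − r)/(1 + e).

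| e | r = 10% | r = 15% | r = 26% |
|---|---|---|---|
| 10% | 1.2 points | 0.7 points | −0.3 points |
| 20% | 2.2 points | 1.3 points | −0.5 points |
| 40% | 3.7 points | 2.3 points | −0.9 points |

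For example, at e = 40% and r = 15%: (0.23 + 0.06)/1.4 = 20.7%, a fall of 2.3 points, or 33% of the 7-point target. A negative entry is a spurious rise, which counts against I-TRANSFER.

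**Step 4: effect on the error rate.** Now let w be the share of the intervention-period cohort that is newly labelled, so p = (1 − w) × 0.23 + w × r. With 869 per period, a two-sided 5% test and no treatment effect, the chance of a significant result favouring I-TRANSFER is Φ(Δ/SE − 1.96). Here Δ = 0.23 − p and SE = √[(0.23 × 0.77 + p(1 − p))/869]. The nominal value is 2.5%.

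- w = 10%, r = 15%: p = 22.2%, Δ/SE = 0.40, chance 5.9%.
- w = 20%, r = 15%: p = 21.4%, Δ/SE = 0.80, chance 12.3%.
- w = 20%, r = 10%: p = 20.4%, Δ/SE = 1.32, chance 25.9%.

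Against a very large control group treated as fixed at 23%, where SE = √[p(1 − p)/869], these become 8.2%, 20.9% and 47.7%. Clustering and covariates are ignored. A model that allows for clustering would have wider standard errors and lower figures, so these show scale only.

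**Step 5: can it explain everything?** The shift in terms of w is w × (0.23 − r). A full 7 points needs w = 7/13 = 54% at r = 10%, or 7/8 = 88% at r = 15%. Relabelling alone is unlikely to mimic the whole planned effect, but it could supply a material part.

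**The case against.** A reader might infer that I-TRANSFER sets out to change hospital sepsis coding. The article does not say this. Its stated goals are identification during the stay and communication to the agency, and its hypothesis about a coded diagnosis concerns the OASIS list in HHC. The Background says "Sepsis survivors are not consistently identified with a medical diagnosis of sepsis until after discharge from acute care", which may be a matter of timing: earlier recognition need not add a claim code. The needs-assessment items are questions about current practice. This objection stands as far as intent goes. What remains is that a change in coding is a foreseeable by-product of working on identification, documentation and accuracy at these hospitals.

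A reader might also infer that newly labelled patients are milder, so that the bias favours I-TRANSFER. The document gives no risk figure for them, and the recommended surveillance definition is described as finding confirmed cases, which does not suggest mildness. The direction is open.

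Three further points have weight. The implicit route shrinks the pool of possible new entrants. Index length of stay, OASIS function, informal support and prior hospitalization do not depend on sepsis coding and may absorb part of a case-mix shift; by how much cannot be known in advance. Checks of this kind are often left to an analysis plan, which is not shown here. If that plan contains them, the point is met. The article does, however, fix the entry rule and list its sensitivity analyses, and none of those would reveal a partner-only change in labelling. Stratifying by type of sepsis describes subgroups but does not test whether their sizes changed.

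**Conclusion.** The concern holds as a risk of selection bias of unknown direction and plausible but unproven size. It rests on three things the article does state: entry by hospital claim codes, an intervention that acts on sepsis identification at partner hospitals only, and a set of planned analyses that does not examine ascertainment. The step from better identification to changed claim codes is an inference.

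If new entrants readmit at 15%, the crude spurious fall is 0.7 to 2.3 points for 10% to 40% extra labelled patients, at most about a third of the target. At 26% it becomes a spurious rise of 0.3 to 0.9 points. All these figures are before covariate adjustment and rest on assumed rates and shares. The documents do not support saying that the treated and control groups differ, or that the result will be biased towards benefit. They support saying that the plan as described could not tell.

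**What to change.** Keep the Aim 1 cohort as defined, and prespecify the following before outcomes are analysed.

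1. **A table of coding shares.** By period, for dyads and for controls, report the share of infection-coded discharges to HHC that carry an explicit sepsis code and the share that carry an organ-dysfunction code. Count an explicit sepsis code as an infection code, so that swapping one label for another does not move a patient in or out of the denominator.
2. **Two sensitivity analyses.** Repeat the primary model, with balancing weights re-estimated, on (a) all infection-coded discharges to HHC and (b) the implicit-rule cohort, whether or not an explicit code is also present.
3. **A reading rule.** State that the effectiveness conclusion will be qualified if these results differ from the primary one. Cohort (a) includes patients outside the intervention's target, so a smaller estimate is expected there. A fair benchmark is the primary estimate multiplied by the baseline share of infection-coded discharges that meet the primary rule.

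Making the implicit rule the primary cohort is not recommended. It would drop explicitly coded survivors whom the intervention is meant to reach, and organ-dysfunction coding could shift too.

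The cost is some extra programming. The data request already covers all Medicare beneficiaries with an HHC claim. The downside is the diluted estimate in cohort (a).
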